### Study procedures

The study procedures are detailed in the study flow chart (refer to Fig 3).

**Fig 3 pone.0324382.g003:**
[figure not shown]
Study flow chart.

We will invite eligible patients for screening through a call and recall system. Visual acuity in both eyes will be recorded using a tablet with a web-based vision checking application (Peek Vision). Non-mydriatic fundus photography of both eyes will be performed using AI-integrated retinal cameras (Forus, 3 Nethra Classic HD with AI Integration in two facilities, and Remidio, Fundus on Phone with AI integration, in two facilities). These AI tools have undergone internal validation and published by the company prior to its integration into the cameras [30,31]. Our project, we will be conducting a real-world validation to assess the performance and effectiveness of this AI tool in practical clinical settings.

Diabetic retinopathy grading will be conducted as per International Clinical Diabetic Retinopathy severity scale [32]. Sight-threatening diabetic retinopathy (DR) is defined as severe non-proliferative diabetic retinopathy (NPDR), proliferative diabetic retinopathy (PDR), and moderate to severe diabetic macular edema (DME). The referral criteria include any patient with DR, visual acuity less than 20/60, any other retinal pathology requiring referral, or ungradable retinal images, or any combination of these factors.

In the AI-enabled screening process for Diabetic Retinopathy (DR) using fundus images, if no signs of DR are detected by the AI, the patient will receive a label of “no DR diagnosis” at the initial stage. However, if DR is indicated, a trained technician at the Idea Clinic will manually review the images to confirm or rule out DR, and the result will be communicated to the patient by the physician. Simultaneously, all images will undergo further manual grading at the Central Image Reading Center at LVPEI for quality assurance. If this manual grading results in a change in diagnosis, the updated result will be shared with the patient within a week since their initial screening.

The images captured at each physician clinic facility will be transferred through a cloud-based teleophthalmology system to the LVPEI central image reading centre (LILAC (L V Prasad eye institute Image Laboratory and Analysis Centre), where grading will be done by two trained graders. Final grading of all referable cases of DR, ungradable images, other pathology needing referral, and an audit of 5% of normal fundus images will be conducted by an experienced ophthalmologist. Patients diagnosed with DR will be referred for appropriate treatment and provided with follow-up advice. Follow-up appointments will be arranged at LVPEI.The follow-up periods for individual participants will be based on the diabetic retinopathy diagnosis and scheduled at 3, 6, and 12 months intervals.

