### Objectives

The study aims to show that systematic screening leads to earlier detection of diabetic retinopathy (DR) and reduces visual impairment. It will compare the effectiveness of screening at physician clinics versus routine DR care in eye care settings. The screening program, supported by trained non-medical technicians, is AI-enabled and targets over 90% accuracy in appropriate referral of DR and 80% coverage of eligible people with diabetes (PWD).

The secondary objectives of the study are to: 1. Assess the cost-effectiveness of the AI-enabled systematic screening program and referral pathway compared to the current pathway at an eye care clinic. 2. Evaluate patient satisfaction and adherence to follow-up recommendations in the AI-enabled screening program versus the routine care pathway through an effective digital tracking system.

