## Methods and analysis

### Study design

We will conduct a prospective cohort study involving a comparison between two patient groups: (i) intervention cohort: patients screened at the diabetes clinics using AI and trained nonmedical technicians and referred to the eye clinic as per the proposed pathway, and (ii) standard-of-care (SOC) cohort: patients who arrive at the ophthalmology clinic as per current practice - either self-walk-ins or referrals from other healthcare providers. Fig 1 shows SPIRIT template for clinical trial.

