### Data management

We will centrally store all study data on a cloud-based data management portal to improve data accuracy and integrity. All data fields will be entered using online spreadsheets to enable seamless entry from both physician and eye clinic sites. A robust data management system will be employed to handle the large volume of data generated, ensuring patient confidentiality and compliance with data protection regulations. The system will facilitate seamless data entry, real-time monitoring, and efficient retrieval of information and tracking of all patients with DR for analysis.

To avoid manual data entry and the need to manage multiple storage platforms and physical consent forms, we will roll out the portal in phases. The first phase will focus on creating a diabetes registry that automates 80% of fields from the IDEA Clinics Electronic Health record (HER) and enables physicians to nominate patients for the Smart DROP Project with a single click from the EHR prescription module. The second phase will introduce digital consent forms and integrate fundus image handling for easier storage and access. The third phase will streamline the Case Proforma, and the portal will also include data visualization through reporting and analytics, as well as communication tools like visit reminders for enrolled patients. The portal will be accessed by designated project users with secure usernames and passwords to ensure confidentiality and data security.

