Provider satisfaction	Proportion of healthcare providers reporting satisfaction with the AI-assisted DR screening program.	Number of providers reporting satisfaction	Total number of providers who completed the satisfaction survey
Follow-up rate	Proportion of patients who return for follow-up visits after initial DR screening or referral.	Number of patients who return for follow-up visits	Total number of patients advised to return for follow-up visits
Long-term outcomes	Proportion of patients with improved visual outcomes or stable DR over a defined period after screening or treatment.	Number of patients with improved visual outcomes or stable DR over time	Total number of patients tracked for long-term outcomes

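### The between-arm comparison of follow-up adherence can be biased: no capture of visits to eye providers outside LVPEI is described, and the two arms are counted from different starting points

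*Protocol article*

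**What the plan says.** All references are to the protocol article.

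- **Objectives**, second secondary objective: the study will evaluate "adherence to follow-up recommendations in the AI-enabled screening program versus the routine care pathway through an effective digital tracking system".
- **Study design**: intervention patients are screened at a diabetes clinic and then referred on to the eye clinic. SOC patients are those who present at the eye clinic, "either self-walk-ins or referrals from other healthcare providers".
- **Study procedures** (below Fig 3): "Follow-up appointments will be arranged at LVPEI", at 3, 6 and 12 months according to the diagnosis. No other place of follow-up is named.
- **Program outcomes, Table 1**: the follow-up rate is the "Proportion of patients who return for follow-up visits after initial DR screening or referral". Its numerator is "Number of patients who return for follow-up visits" and its denominator is "Total number of patients advised to return for follow-up visits". No site is specified, and visits to other providers are not classified.
- **Data management**: data are entered from the study's physician and eye clinic sites. Patients with DR are tracked, and the portal will include "communication tools like visit reminders for enrolled patients". Whether tracking extends to visits outside the study sites is not stated.

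The article gives no expected adherence rate and no figure for attendance at other eye providers.

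**The concern.** A patient screened at a diabetes clinic who takes the referral to a different eye doctor has acted on the advice. With appointments arranged at LVPEI and data entered from the study sites, no described source would show that visit. The natural working reading of the Table 1 numerator is then a return to LVPEI. SOC patients selected LVPEI before they could be enrolled, so the same loss plausibly affects them less.

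At stake is the meaning of a secondary objective. A lower rate in the intervention arm could reflect poorer adherence, care obtained elsewhere, or the extra step from diabetes clinic to eye clinic that only this arm has to make. A true benefit could be hidden or a false deficit created. The remedy lies in data collection: if nobody asks about outside visits, no later analysis can recover them. According to the Study timeline section, recruitment began in March 2024.

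**Working it through.** **1. Is there a stated figure to reproduce?** None for adherence. The nearest is the sample size for disease staging, 60 per arm. With 50% against 25%, two-sided 5% and 80% power, the pooled normal formula without continuity correction gives 58, and power at 60 per arm is 81.6%. That figure reproduces, but it does not bear on adherence. Below, 60 per arm serves only as a yardstick.

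**2. Starting points side by side.**

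| | Intervention | SOC |
|---|---|---|
| Entry (Study design) | Screened at diabetes clinic | Already at the eye clinic |
| Can be counted from (Table 1) | Screening or referral | After reaching LVPEI |
| Step still to make | First move to LVPEI, then returns | Returns only |

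**3. Effect of unrecorded outside visits.** Let *a* be true adherence, equal in both arms, and let *e_I* and *e_S* be the shares of adherent patients who attend elsewhere and are recorded as not returning.

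- Observed rate = *a* × (1 − *e*)
- False difference (intervention minus SOC) = *a* × (*e_S* − *e_I*)

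Every input here is assumed. The last column is the approximate chance of a two-sided p < 0.05 with 60 per arm when true adherence is equal.

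| *a* | *e_I* | *e_S* | Intervention observed | SOC observed | False difference | Chance of p < 0.05 |
|---|---|---|---|---|---|---|
| 60% | 10% | 0% | 54% | 60% | −6 points | 10% |
| 60% | 20% | 0% | 48% | 60% | −12 | 26% |
| 60% | 30% | 0% | 42% | 60% | −18 | 51% |
| 60% | 10% | 5% | 54% | 57% | −3 | 5% |
| 60% | 30% | 5% | 42% | 57% | −15 | 37% |
| 80% | 10% | 0% | 72% | 80% | −8 | 17% |
| 80% | 30% | 0% | 56% | 80% | −24 | 81% |

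Two further cases show how far the result depends on the assumed shares:

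- Equal shares: *a* × 0 = 0 points.
- Shares reversed, *e_I* = 10% and *e_S* = 20%: 0.60 × (0.20 − 0.10) = +6 points, in favour of the intervention.

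**4. Effect of the different starting point.** Let *r* be the proportion of referred intervention patients who complete the first eye visit, and *f* the later return rate among patients already seen. A rate for later visits counted from referral is *r* × *f* in the intervention arm, against *f* in SOC. The two differ even when *f* is equal and nobody goes elsewhere.

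The Sample size section suggests that *r* may be well below 1. It assumes sight-threatening DR (STDR) of about 10% at screening and about 25% among those who complete the first eye visit, because early-stage patients may not comply. Per 100 DR patients at screening, if a proportion *c* of the 10 with STDR complete the visit, total completers = 10*c* / 0.25 = 40*c*, so at most 40. This takes both percentages as among DR patients and assumes no change of stage between the two visits. It bounds planned first-visit completion. It says nothing about how many of the remainder obtain care elsewhere, and so does not give the size in step 3.

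**5. Can the planned analysis repair it?** The Ethics section provides for sensitivity analyses, multiple imputation or last observation carried forward. Outside attenders would look the same as patients lost to follow-up, and none of these methods can tell the two apart without a recorded variable.

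**The case against.** **The error is inferred.** A reader might conclude that follow-up takes place only at LVPEI and that a patient seen elsewhere is scored non-adherent. The article says neither. Table 1 is silent on site, a digital tracking system is planned, and an article may leave such detail to the full protocol. This stands, and it is why the point is put as a risk. It does not remove the risk: the article does set out the outcome's numerator and denominator, describes appointments at one institution only, and compares the result between arms.

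**Attendance at LVPEI may be the intended outcome.** The intervention is a defined pathway, and leaving it is informative. This stands for a pathway-completion measure, which should be kept. It does not settle the stated objective, which compares adherence to recommendations with routine care.

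**The direction is not established.** The Selection of participants section lists ophthalmologists among the SOC referral sources, and those patients may return to the doctor who sent them. Intervention patients remain in contact with a diabetes clinic that enters study data, so their outside visits might be easier to learn about. This stands.

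**The magnitude follows from the assumptions.** Taking 10–30% outside attendance in one arm and 0–5% in the other guarantees a deficit. This stands; the table shows sensitivity and is not an estimate.

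**Missing disease stage.** A reader might also infer that intervention patients first seen elsewhere have no recorded stage. That goes too far: all screening images are graded at the central reading centre, so stage at screening is on record.

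**Conclusion.** The concern holds as a risk of differential misclassification in the adherence comparison. It rests on three features of the text: follow-up visits are described only as appointments arranged at LVPEI, no capture of visits to other eye providers is described, and the follow-up rate can start at screening or referral in one arm but only after arrival at LVPEI in the other.

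The documents do not establish that outside attendance is counted as non-adherence, nor the size or sign of any bias. A deficit for the intervention is the likelier direction because SOC patients have already selected LVPEI. It would vanish if outside shares were equal and reverse if more SOC patients went elsewhere. The illustrative 3 to 24 points depend wholly on assumed adherence of 60–80% and assumed outside shares of 10–30% against 0–5%. The point is worth correcting because the correction is cheap and the missing information cannot be recovered later; it does not threaten the staging comparison.

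**What to change.** 1. Define follow-up adherence as attendance at any eye-care provider within the advised window, and apply that definition to both arms.
2. Ascertain it identically in both arms: the LVPEI record, plus one question in the planned tracking or reminder contact on whether, and when, the patient has seen an eye doctor elsewhere.
3. Report attendance at LVPEI separately, as pathway completion.
4. In the intervention arm, report completion of the first referral visit on its own. Compare later follow-up between arms only among patients who have completed a first eye visit, so that both arms start from the same point. State that this comparison is conditional on having reached eye care.

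The cost is one question in a contact that is already planned and one field in the portal. The drawback is that outside visits are self-reported and unverified, so the any-provider and LVPEI-only rates should be shown side by side. Patients already enrolled would need to be asked retrospectively, or analysed with their outside attendance marked as unknown.

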### Study timeline

Following the approval of our clinical trial registration by the Clinical Trials Registry of India (CTRI) (https://ctri.nic.in) on March 20, 2024, we commenced patient recruitment on March 29, 2024. Currently, recruitment and data collection are ongoing at both the intervention arm (Idea Clinics) and the standard-of-care arm (LV Prasad Eye Institute). An interim data analysis is scheduled for one year from the recruitment start date. The total duration of the project is three years.

### Quality assurance, quality control measures

To ensure rigorous quality assurance and control, the study will include comprehensive technician training with quarterly refreshers and bi-monthly calibration of AI screening equipment. Comprehensive training programs will be provided to non-medical technicians, focusing on the correct use of AI-assisted screening equipment, standardized procedures for visual acuity tests, and accurate capture of fundus photographs. Technicians at diabetes clinics will be trained in visual acuity estimation and validation tests (n = 25) to ensure reliability and accuracy. The visual acuity tool used in the study (Peek Vision) has been globally validated in multiple studies and effectively utilized by technicians and field workers in diverse settings [33,34]. The sample size of **N = 25 patients (50 eyes)** is intended for pilot testing following standardized training. This pilot will serve as an initial assessment of the reliability and accuracy of visual acuity estimation using the mobile VA application by trained technicians. The pilot testing results will be used to validate the training protocol and identify any gaps requiring refinement.

To ensure ongoing reliability, periodic audits will be conducted during training refresher programs, where technicians’ performance will be re-evaluated. Additionally, comparisons of visual acuity estimates from referred patients will be performed to assess consistency over time. This iterative approach ensures that the quality of visual acuity measurements is maintained throughout the study. They will also receive training in fundus image capture, study image protocol, DR grading and referral criteria.

Quality control measures will be implemented to monitor and verify the accuracy of DR and STDR detection rates, timely referral rates, and other key metrics. A quality assurance process will compare AI grading with manual grading by the technician and the Central Reading Center to ensure screening accuracy and reliability.

Weekly audits will validate 5% of normal fundus images, review all DR and retinal pathology, ungradable cases, and ensure adherence to screening protocols. Monthly physical visits to diabetes clinics will monitor protocol compliance, and both weekly team reviews and monthly investigator meetings will assess project performance and outcomes. Patient outcomes will be cross-referenced with established benchmarks (e.g., National DR screening guidelines) to verify the accuracy of DR detection.

### Data management

We will centrally store all study data on a cloud-based data management portal to improve data accuracy and integrity. All data fields will be entered using online spreadsheets to enable seamless entry from both physician and eye clinic sites. A robust data management system will be employed to handle the large volume of data generated, ensuring patient confidentiality and compliance with data protection regulations. The system will facilitate seamless data entry, real-time monitoring, and efficient retrieval of information and tracking of all patients with DR for analysis.

To avoid manual data entry and the need to manage multiple storage platforms and physical consent forms, we will roll out the portal in phases. The first phase will focus on creating a diabetes registry that automates 80% of fields from the IDEA Clinics Electronic Health record (HER) and enables physicians to nominate patients for the Smart DROP Project with a single click from the EHR prescription module. The second phase will introduce digital consent forms and integrate fundus image handling for easier storage and access. The third phase will streamline the Case Proforma, and the portal will also include data visualization through reporting and analytics, as well as communication tools like visit reminders for enrolled patients. The portal will be accessed by designated project users with secure usernames and passwords to ensure confidentiality and data security.

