### Selection of participants

The inclusion criteria for this study in the intervention arm are People with Diabetes (PWD) who visit the diabetes clinics who have never had a fundus examination or fundus photo screening IDEA clinics (Diabetes clinics)/LVPEI(Eye clinics). The referral source will be captured as self-reported, physician, LVPEI network, or ophthalmologist in the standard of care arm -LVPEI eye clinic pathway.

The exclusion criteria for the study are designed to omit individuals with previously diagnosed Diabetic Retinopathy (DR) at the time of presentation to diabetes clinics during the study period. Although we will not include the images of these patients in the study analysis, we will offer appropriate care for their DR at the eye clinic. Additionally, we will seek consent from all eligible participants before they are enrolled in the study and subjected to study protocol. Participants enrolled in the project will be between 18 and 90 years of age.

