### Sampling

The study will employ a **convenience sampling method**, recruiting all consecutive eligible individuals with diabetes mellitus (DM) visiting physician clinics and eye care settings who meet the standard inclusion and exclusion criteria and provide informed consent. While convenience sampling is utilized, potential sources of bias include **selection bias, site-specific variation, differential access to care and Observer Bias**. To mitigate these, systematic recruitment will be ensured by enrolling all eligible patients consecutively at each site, reducing the likelihood of preferential selection. Recruitment will take place across multiple physician clinics and eye care settings to improve representativeness and minimize site-specific variation. Differential access to care will be monitored by assessing demographic and clinical characteristics of enrolled participants, allowing adjustments to recruitment strategies if needed. To prevent observer bias, standardized screening protocols and training for healthcare personnel will be implemented, ensuring consistency in recruitment and data collection. These measures aim to enhance the validity and generalizability of the findings while acknowledging the inherent limitations of convenience sampling.

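### Unscreened IDEA patients can be counted as standard-of-care controls, and no rule ties physician nomination to the claimed consecutive enrolment

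*Protocol article*

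**What the plan says.** The Sampling section of the protocol article describes "recruiting all consecutive eligible individuals with diabetes mellitus (DM) visiting physician clinics and eye care settings". It names selection bias as a risk and answers it as follows: "systematic recruitment will be ensured by enrolling all eligible patients consecutively at each site, reducing the likelihood of preferential selection".

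Two entry routes at the diabetes clinics are described elsewhere. Under Study procedures: "We will invite eligible patients for screening through a call and recall system". Under Data management, the first phase of the portal builds a registry fed largely from the IDEA health record and "enables physicians to nominate patients for the Smart DROP Project with a single click from the EHR prescription module".

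The SOC cohort is defined under Study design as "patients who arrive at the ophthalmology clinic as per current practice - either self-walk-ins or referrals from other healthcare providers". Under Selection of participants: "The referral source will be captured as self-reported, physician, LVPEI network, or ophthalmologist in the standard of care arm". No SOC criterion mentions attendance at an IDEA clinic. The Ethics section adds that, at LVPEI, the written consent given for the routine comprehensive examination is taken as study consent.

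The study is sized on disease stage at the first eye consultation: STDR among patients with DR of 50% in SOC against 25% in the intervention arm, with 60 per arm (Sample size).

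**The concern.** Consecutive enrolment protects against selection only if something makes it happen. Physician nomination is, as described, a choice made by the treating physician. The article does not require every eligible patient to be nominated, and it does not require a reason to be recorded when one is not.

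The second half of the problem is at LVPEI. Take an IDEA patient with no previous fundus examination who is overlooked, declines screening, or is sent directly to the eye clinic. On arrival that patient fits the SOC definition as a walk-in or a physician referral. The referral-source field does not separate IDEA physicians from other physicians, and a self-referred decliner leaves no trace of IDEA attendance. Because routine consent suffices, someone who declined at IDEA can enter SOC without being asked again about the study.

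At stake is the staging comparison. If patients with visual symptoms are the ones who bypass screening, they leave the intervention arm and join the controls. Both proportions then shift in the intervention's favour, and patients whom the programme failed to reach count as evidence for it.

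**Working it through.** **1. The plan's own figure.** Inputs from Sample size: p1 = 0.50, p2 = 0.25, power 80%, type I error 5% (two-sided assumed, since the article does not say).

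n = [1.96·√(2·0.375·0.625) + 0.842·√(0.25 + 0.1875)]² / 0.25² = 58 per arm with pooled variance. Power at 60 per arm is 81.6%. The stated 60 is reproduced to within two patients, so this point does not touch the sample-size arithmetic.

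**2. How many IDEA patients with DR are expected not to consent.** The article's chain is 60/0.80 = 75 with DR, and 75/0.20 = 375 registered and screened. Read forwards, 375 × 0.20 = 75 with DR, 75 × 0.80 = 60 consent, and 75 − 60 = 15 do not. How many of the 15 would present at LVPEI is unknown. Patients who are never nominated are not covered by this figure.

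**3. Effect of patients changing arm.** Assumptions: no true effect, and 24/60 (40%) STDR in each arm. If m patients move, of whom s have STDR, the arms read (24 − s)/(60 − m) v (24 + s)/(60 + m).

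| Movers m | With STDR s | Intervention | SOC | False gap |
|---|---|---|---|---|
| 6 | 6 (worst case) | 18/54 = 33.3% | 30/66 = 45.5% | 12.1 points |
| 6 | 4 | 20/54 = 37.0% | 28/66 = 42.4% | 5.4 points |
| 6 | 2.4 (the 40% average) | 21.6/54 = 40% | 26.4/66 = 40% | 0 |

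The design difference is 25 points. The worst-case row is not itself significant: z = 0.1212/√[0.4·0.6·(1/54 + 1/66)] = 1.35, p about 0.18.

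**4. Separating the two halves of the problem.** Assumptions, none of them from the article: no true effect; 35% STDR among DR patients in both source populations; IDEA enrolment of 60% for STDR and 90% for other DR. Overall enrolment is then 0.35·0.60 + 0.65·0.90 = 79.5%, close to the article's 80%.

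- Intervention arm: 0.21/0.795 = 26.4% STDR.
- Missed among 75 IDEA patients with DR: 75·0.35·0.40 = 10.5 with STDR and 75·0.65·0.10 = 4.875 without.
- SOC arm (60 patients from outside IDEA, plus none, half or all of those missed): 21/60 = 35.0%, 26.25/67.69 = 38.8%, 31.5/75.375 = 41.8%.
- False gap: 8.6, 12.4 or 15.4 points. With 60 per arm, the chance of a significant result favouring the intervention is 17%, 30% or 43%, against a nominal 2.5%.

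The 8.6 points arise with no leakage into SOC at all, so excluding IDEA patients from SOC removes only the part above that. With enrolment of 80% at every stage, the gap is zero throughout.

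**The case against.** The strongest reply is that the article does not say what a quick reading suggests.

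- **Nomination as the gateway.** A reader might infer that IDEA patients enter only by physician nomination, so that enrolment is not consecutive. The text does not support this. Nomination is a function of a data portal, call and recall is also described, and one-click nomination is compatible with nominating everyone eligible. What stands is narrower: no rule connects these routes to the consecutive enrolment that Sampling relies on.
- **Advanced cases move to control.** A reader might take this as established. It is inference. Intervention patients have never had a fundus examination, so their stage is unknown at nomination, and no stage-dependent rate is given. Symptoms and poor vision, however, are apparent before screening, so the mechanism is plausible.
- **Number of decliners.** Dividing 375 by 0.80 again gives 469 eligible, 94 decliners and 19 with DR. That applies the consent rate twice; the article's own chain gives 15.
- **Adjustment.** Baseline visual acuity is a named covariate under Statistical analysis and may absorb part of the bias. It cannot return a patient to the right arm, and acuity may itself reflect late detection.
- **Other safeguards.** Table 1 measures uptake over all eligible patients, so unreached patients count against the programme there. That is a separate outcome and does not alter the staging comparison.
- **Pathway definition.** An unscreened IDEA patient who walks into LVPEI did receive current practice, so counting that patient as SOC can be defended. But the patient also belongs to the population that the programme was meant to cover, and the article does not address the overlap.
- **Condensed article.** Operational detail may sit in the full protocol. Arm definitions and the means of controlling selection are, however, stated here, and as stated they leave the overlap open.

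**Conclusion.** The point holds in a limited form. Consecutive enrolment is the stated means of reducing preferential selection at recruitment, and nothing in the article ties physician nomination to it. The SOC definition, the referral-source categories and the LVPEI consent rule together allow an unscreened IDEA patient to be counted as a control without being identified.

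Whether this biases the result depends on whether bypassing screening is related to stage, which the article does not inform. If it is unrelated, this bias is zero. If those who bypass carry more STDR, the staging comparison tilts towards the intervention. For six movers the illustration runs from no gap, through 5.4 points, to a worst case of 12.1 points, against a design difference of 25. These figures show sensitivity; they do not estimate what will happen. The article does not support saying that advanced cases will move, or that enrolment is in fact selective. The change is worth making while recruitment continues: without a record of IDEA attendance, the sponsor could not show that the overlap is absent or small.

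**What to change.** 1. Use the registry, which already draws most of its fields from the IDEA health record, to flag every attending patient who meets the criteria under Selection of participants, in place of discretionary nomination. Log the reason whenever a flagged patient is not screened.
2. At LVPEI intake, record whether a SOC patient has been registered at any of the four IDEA clinics since recruitment began on 29 March 2024. Exclude such patients from the SOC arm of the staging comparison.
3. For SOC patients already enrolled, identify those who are IDEA patients and repeat the staging comparison without them.

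The cost is a portal rule, one intake question and one SOC criterion by amendment, with a few SOC patients lost and a short log to keep. The exclusion removes contamination of SOC but does not restore missed patients to the intervention arm. That is why the flag and the log are needed as well.
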